#### Program acceptability, feasibility, and process evaluation

Quantitative and qualitative assessments of intervention acceptability and satisfaction will be collected from parents and providers/staff. For parents, we will administer self-report surveys (*n* = 60 per clinic) after they receive referrals and engage in nutrition support programs for 6- and 12-months. A random sample of parents (*n* = 10 per clinic, using a purposeful sampling method to include parents who successfully accessed programs and those who did not) will be invited to participate in a post-interview. The post-interviews will be conducted using a semi-structured interview guide probing relevant PRISM domains such as parents’ experience, usefulness, satisfaction, and recommendations for improvements with each program component, including concerns or barriers to accessing the CBOs, and interactions with health care providers, care navigators, and CBOs.

Providers, care navigators, and key health care administrators will also be invited to participate in a 45–60 minute group-based periodic reflection [34] (per active clinic) to determine challenges, opportunities, and modifications needed to optimize program implementation for the subsequent clinic roll-out. All participants will be invited to complete post-roll-out surveys (every 6 months) to assess impact, feasibility, acceptability, and appropriateness or fit of the program using the 4-item Acceptability of Intervention Measure (AIM), Intervention Appropriateness Measure (IAM), and Feasibility of Intervention Measure (FIM)) [60]. All interviews and periodic reflections will be audiotaped and transcribed verbatim for analysis.

At the community partner level, focus groups or key informant interviews will be conducted to determine the impact of referrals on their program (e.g., were they able to meet the increased demand) and what further improvements in communication are needed between the health care system and families. Final workflows and systems will be reviewed and refined by community stakeholders before being utilized in a fully-powered clinical trial.

#### Program fidelity and reach

Fidelity to intervention components and implementation outcomes will be tracked. Care navigators will document the following: whether they were able to contact a family who screened positive for FI, whether the parent was open to receiving referrals to nutrition support programs, whether follow-up phone calls were made to check on progress and program utilization, and whether additional referrals were needed. This information will also help us to determine the reach of the program and how many families were able to participate compared to the overall number of families who screened positive for FI.

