Aim 1 Implementation Mapping and Optimization	• Adaptations and Implementation strategies • Barriers to program implementation • Structures and systems needed to implement program and support community programs • Experience with multi-component implementation • PRISM Fit assessment	H, Com H, Com H, Com P, H, Com P, H, Com	Periodic reflection, Interviews Periodic reflection, Interviews	Before, during, after each roll-out Before, during, after each roll-out
Aim 2 Implementation Outcomes	• Acceptability, Feasibility, Appropriateness of program [60] • Reach: % of families attending clinic that completed screener, # of families in the registry, % of families that did not want service, Characteristics of participating vs. non-participating families • Adoption: Characteristics of clinic settings and staff, Characteristics of community program (location, months/days/hours of operation, description of benefits or incentives, educational programs available) • Readiness for organizational change scale [61] • Implementation Climate Scale [62] • Implementation/Fidelity: % of families that were called, % of families that were referred or provided with resources, % of families that received follow-up phone calls, % of families that needed additional resources/referrals • Maintenance: • Program Sustainability Index [63] • Perceived support of innovation in organizations [64] • Partnership synergy tool [65–67]	P, H, Com H H, Com H H, Com	Periodic reflection, Interview, Survey EHR, Survey Survey, Periodic reflection EHR, Periodic reflection Survey	6, 12 mos Ongoing & 12 mos Ongoing & 12 mos Ongoing & 12 mos 12 mos

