#### Medical record abstraction

EHR data will be used to track preliminary clinical effectiveness outcomes (Aim 3). EHR data will be used to track patient health outcomes (e.g., BMI, HbA1c, LFTs, cholesterol), SDOH outcomes, medication adherence, health care utilization (e.g., follow-up visits made to primary care or subspecialty physicians, adherence to appointments, ED visits, hospitalizations, lab orders, medications prescribed), and I-FRESH program process measures (e.g., phone call attempts by the care navigator, referrals made to community nutrition support programs). Demographic information (i.e., age, sex, race, ethnicity, insurance status) will be collected to examine if there are differences between those who engage in the program and those who do not.

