#### Quantitative data

Primary analyses for Aim 2 will assess fidelity and reach outcomes (Aim 2b) assessed within the EHR (e.g., screening, referrals, and follow-up assessments) and surveys (e.g., Acceptability, Feasibility, and Appropriateness) across the study period using Generalized Linear Mixed-effects Models (GLMM) and time-varying indices for clinics randomized to cross-over in each wave, time (secular trend), and clinic characteristics as planned covariates. Serial cross-sectional summaries for each clinic within monthly blocks will allow estimation of changes in clinic outcomes after crossing over into interventions. Primary analyses for Aim 3 will describe I-FRESH participants’ (*n* = 240) changes in health outcomes including: a) metabolic labs, BP, BMI, b) healthcare utilization; c) community program utilization; d) Quality of Life; e) Food Frequency Questionnaire and f) Knowledge, Skills, Attitudes, and Self-Efficacy. GLMM growth models for individual trajectories of continuous and limited categorical outcomes will include a focus on significance of changes from baseline to post-treatment assessments after graphically examining an appropriate functional form (e.g., linear or categorical) for modeling each outcome. All models will include participants’ characteristics (gender, ethnicity, parental education) and allocation clinic as planned covariates when estimating changes in primary health and engagement outcomes. We will explore the role of SDOH and implementation strategy effectiveness as potential influences in describing changes in parent and child health outcomes. Benjamini-Hochberg [78] procedures will be used to adjust *p*-values for inference decisions within common domains.

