##### Power considerations

We conducted power/sample size for this ROIO design trial to address primary aims, using developed formulas [81] drawn from stepped wedge designs that account for unequal cluster size and package *swCRTdesign* [82]. The design includes 4 identified clinics (clusters), at least one 3-month period in standard care and 4 additional periods where assigned clinics can transition to I-FRESH at 4-month intervals. We estimated the needed sample to test a 10% difference in proportions of engagement in services (i.e., Aim 2b healthcare and community program utilization), and a standardized mean increase of at least d ≥ 0.20 when reported at 6- and 12-month health outcomes. With alpha = 0.05, 4 clusters (1 clinic per cluster = 4 clinics with *n* = 300 - 500 potential patients in each clinic) and five periods of transitions (baseline and 4 clinics), we will maintain power > 0.83 to detect clinic differences (I-FRESH vs standard care) of >8% in rates of screening, referral and follow-up engagement in services and changes in acceptability ratings of d > 0.20 after implementing I-FRESH given a between clinic standard deviation of 0.05 in random treatment effects. Using an empirical approach, we simulated 1000 data sets with expected mean changes (d ≥ 0.20) and serial correlations similar to pilot samples. We used the percentage of growth models with *p* < 0.05 for slope parameters to estimate power given proposed sample of 60 per clinic and allowance for 20% missing data. With median slope of 0.02 (increase per month; estimate sd = 0.01) we observed significant effects in >81% of models suggesting sufficient power to detect desired effects in Aim 3 with the proposed sample.

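### Referral and follow-up are to be compared with standard care, but calls and community referrals are defined as I-FRESH process measures and no standard-care source is stated for them

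*Protocol article*

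**What the plan says.** All places are in the protocol article.

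- **Analysis.** Quantitative data makes EHR-assessed fidelity and reach outcomes (screening, referrals and follow-up assessments are the examples) primary for Aim 2, in a mixed model with cross-over, time and clinic terms. Monthly clinic summaries "will allow estimation of changes in clinic outcomes after crossing over into interventions".
- **Power.** Power considerations claims power above 0.83 "to detect clinic differences (I-FRESH vs standard care) of >8% in rates of screening, referral and follow-up engagement in services".
- **Who records.** Program fidelity and reach states "Care navigators will document the following" and then lists contact with families who screened positive, openness to referral and "whether follow-up phone calls were made to check on progress and program utilization, and whether additional referrals were needed". The initial referral is not on the list.
- **How the measures are classed.** Medical record abstraction names "I-FRESH program process measures (e.g., phone call attempts by the care navigator, referrals made to community nutrition support programs" among the EHR items. Table 1 places the percentage called, the percentage referred and the percentage "of families that received follow-up phone calls" under Implementation/Fidelity.
- **What exists before cross-over.** Setting and context says that the two-item food-insecurity screener has been in the EHR since 2020. The patient registry is to be created for the study (Screening and identification). It will cover all patients of the participating clinics, and the proportions it is said to supply are screener completion and positive screens (Measures, text after Table 1).

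**The concern.** The same quantities serve two purposes that do not fit together. As fidelity measures, they ask whether the program's components were delivered once the program was running. As outcomes of the cross-over model, they need a standard-care value measured in the same way.

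Referral help and the follow-up call are themselves components of I-FRESH, and navigators document contact and follow-up calls. If both the activity and its recording begin at cross-over, a rise may reflect more care, the arrival of the program's own call step, or better recording. The planned analysis cannot tell these apart.

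The results are meant to guide a fully powered hybrid effectiveness-implementation trial. An effect inflated by recording would carry over into that trial's assumptions and its choice of strategies.

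**Working it through.** **1. The plan's own figure, for context.** The stated power is above 0.83 for a difference of more than 8 points. I used a stepped-wedge linear mixed model with 4 clinics, 5 periods, one clinic crossing per step, fixed period effects, a random-treatment-effect SD of 0.05 (stated) and a two-sided test at 0.05 (sidedness assumed). The standard-care rate (5–50%), the clinic-intercept SD (0–0.10) and the meaning of n = 300–500 are not given, so I varied them.

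- n per clinic-period: power for 8 points is 0.65–0.85. It reaches about 0.83 only at low standard-care rates, for example 0.826 (n = 400) and 0.839 (n = 500) at a 5% rate with intercept SD 0.05.
- n as the clinic total over five periods: 0.29–0.70.

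The figure is attainable under favourable assumptions but cannot be confirmed. The point below does not depend on it.

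**2. Sources side by side.**

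| Measure | Class or recorder in the article | Standard-care source stated? |
|---|---|---|
| Screener completion | EHR tool in place since 2020 | Yes |
| Healthcare utilization (visits, appointments, ED) | Routine EHR data | Routine record in both phases |
| Community referral | I-FRESH process measure, EHR | No |
| Contact, follow-up calls, need for further referrals | Documented by navigators | No |

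**3. Why the model cannot separate the two.** Suppose program recording starts when a clinic crosses over. The indicator for recording is then the same 0/1 column as the indicator for I-FRESH, clinic by clinic and month by month. The cross-over coefficient estimates the sum of the change in care and the change in recording. Clinic and time terms do not help, because the staggered dates are the same for both.

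**4. Possible size for referral.** Let p be the true referral rate, equal in both phases, and s the share recorded in standard care. Assume full recording under I-FRESH.

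Apparent difference = p − p·s = p(1 − s)

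- p = 0.30, s = 0.70: 0.30 × 0.30 = 0.09
- p = 0.30, s = 0.50: 0.30 × 0.50 = 0.15
- p = 0.20, s = 0.90: 0.20 × 0.10 = 0.02
- p = 0.50, s = 0.50: 0.50 × 0.50 = 0.25

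The capture share at which recording alone gives 8 points is s = 1 − 0.08/p: 20% at p = 10%, 60% at p = 20%, 73% at p = 30% and 84% at p = 50%.

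**5. Chance of a significant result from recording alone.** Same model, with n = 400 per clinic-period and intercept SD 0.05 (both assumed):

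| True rate p | s = 50% | s = 75% | s = 90% |
|---|---|---|---|
| 20% | 0.93 | 0.40 | 0.10 |
| 30% | >0.99 | 0.69 | 0.16 |
| 50% | >0.99 | 0.97 | 0.34 |

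Neither p nor s is given in the article, so steps 4 and 5 show what could happen, not an estimate of what will.

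**The case against.** The strongest reply has four parts.

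- **Referral is not navigator-recorded.** The navigator list omits the initial referral, referrals are drawn from the EHR, and the Readiness assessment section lets physicians, nurses, social workers or others hold the discussion. This stands. A reader might infer that every referral is counted only through a navigator entry; the article does not say so. What remains is that referral is called an I-FRESH process measure and has no stated standard-care source.
- **The powered outcome is wider than phone calls.** Power considerations explains engagement in services as healthcare and community program utilization, and healthcare utilization is routinely recorded in both phases. This stands, and those outcomes are outside the concern. It does not remove the problem, because Quantitative data puts fidelity outcomes, with referrals and follow-up named, into the cross-over model.
- **Nothing shows that standard care has no calls or poorer records.** This also stands. A reader might infer that the standard-care call rate is zero by definition, or that referrals are certainly under-recorded before cross-over. Both are inferences: some usual-care staff may call families, and existing orders or notes may capture referrals. But if there are no such calls, the contrast shows only that the program started; if there are some, no stated source counts them.
- **A rise in delivery is a legitimate implementation result, and family benefit belongs to Aim 3.** Agreed. Delivery after cross-over can be reported directly as fidelity. A test against standard care adds information only if both phases are measured alike.

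The point is not a complaint about detail left to a fuller document. The article itself fixes the measures, the recorder of the calls and the contrast.

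**Conclusion.** The concern holds in limited form. Navigator contact and follow-up-call rates have no like-for-like standard-care value, so a between-condition test of them mainly confirms that the program began. The referral contrast may be inflated. The size is 9–15 points at an assumed 30% rate and 50–70% standard-care capture, and 2–25 points over assumed rates of 20–50% and capture of 50–90%, set against the 8-point target. The bias is small if standard-care capture is nearly complete, which the article does not claim. All these figures assume no true change and full recording under I-FRESH; with less than full recording they shrink.

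The documents do not support saying that the referral comparison is certainly biased, or that screening and routine healthcare utilization share the problem.

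**What to change.** Limit the cross-over mixed model, and the I-FRESH versus standard care power statement, to outcomes captured the same way in the EHR in both conditions: screener completion, routine healthcare utilization, and referrals only if the same EHR order or field identifies them before and after cross-over. State that field.

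Report navigator contact, follow-up-call and additional-referral rates after cross-over only, by clinic, as fidelity proportions with confidence intervals.

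The cost is a change of analysis wording and fewer outcomes with a between-condition test. No data are lost and the intervention is unchanged.

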#### Medical record abstraction

EHR data will be used to track preliminary clinical effectiveness outcomes (Aim 3). EHR data will be used to track patient health outcomes (e.g., BMI, HbA1c, LFTs, cholesterol), SDOH outcomes, medication adherence, health care utilization (e.g., follow-up visits made to primary care or subspecialty physicians, adherence to appointments, ED visits, hospitalizations, lab orders, medications prescribed), and I-FRESH program process measures (e.g., phone call attempts by the care navigator, referrals made to community nutrition support programs). Demographic information (i.e., age, sex, race, ethnicity, insurance status) will be collected to examine if there are differences between those who engage in the program and those who do not.

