## Methods

Using the ROIO design, we will engage our CARAB to refine and optimize implementation of the I-FRESH program before and after each roll-out in 4 clinics at Rady Children’s Health in San Diego: diabetes, gastroenterology, preventive cardiology, and severe asthma clinic. Periodic Reflections [34] will be held before, during, and after implementation in each of the 4 clinics with CARAB to determine which refinements or adaptations should be made to increase adoption and improve implementation of this workflow. Using the PRISM framework, this group will identify factors in the inner and outer context that serve as barriers and facilitators to I-FRESH implementation and family engagement in the program (Aim 1). Using Implementation Mapping [35] processes, we will refine an effective implementation process model for our healthcare system. We will also assess implementation outcomes of the I-FRESH program using the RE-AIM outcomes framework [32, 33] (Aim 2). Finally, we will examine preliminary effect on family-level food security and pediatric nutrition-related health outcomes (Aim 3). The I-FRESH study was approved by the UC San Diego IRB (protocol # 810869).

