### Participants

Members of the CARAB (which includes health care providers, hospital administrators, population health/public health leaders, staff from community-based organizations (CBOs), food as medicine experts, equitable food systems collaborative leaders, community members, community health workers, and the research team) will be invited to provide their views and opinions on how the program is functioning and complete RE-AIM assessments. Our goal is to recruit up to 100 health care staff and CARAB stakeholders to complete Aims 1 and 2. Up to 10 parent participants per clinic (*n* = 40) who are 18 years or older will also be asked to participate in Aims 1 and 2. These parents/caregivers will have a child with a nutrition-related condition who attends one of the 4 participating clinics and screens positive for FI.

To study the impact of this program on family-level FI and pediatric nutrition-related health outcomes (Aim 3), we plan to recruit 240 parents of a child aged 0–18 attending one of the participating clinics (~60 per clinic). These families will screen positive for FI based on the 2-item Hunger Vital Sign [40].

Exclusion criteria will be limited given the heterogeneous nature of the populations in each clinic. This will increase generalizability of our findings and allow us to explore a wide range of implementation issues before testing this program in a larger type 2 hybrid effectiveness-implementation trial. We will track the following variables and include them as covariates or moderators rather than exclusion criteria: 1) child medical conditions for which physician supervision of diet are needed; 2) child body mass index (BMI) percentile; 3) child medications; 4) family language preferences; 5) family household size and composition; and 6) other SDOH factors (e.g., lack of housing or transportation) that would impact the family’s ability to access nutrition support programs.

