#### Specific Aim 3: Examine preliminary impact and effectiveness outcomes

We will further apply RE-AIM and examine exploratory clinical effectiveness outcomes including family-level FI and pediatric nutrition and metabolism-related health outcomes that may be similar across the different clinics: weight status, blood pressure (BP), lipids, HbA1c, and liver function tests. We will also assess changes in medication dose or type (e.g., stopping insulin and only requiring metformin) and engagement with the clinic or recommended services (e.g., decrease in no-show rates). While the larger goal of the program is to decrease FI and improve health outcomes, we will also collect information on the family’s self-reported knowledge, skills, attitudes (expectancies), self-efficacy, and social support needed to engage in the program. Other behaviors of interest include consumption of and barriers to consuming fruits and vegetables.

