Aim 3 Effectiveness Outcomes	• Health outcomes: BMI/weight status, HbA1c, blood pressure, total cholesterol, HDL cholesterol, liver function, health status • Quality of life, stress, well-being • PRAPARE (patient assets, risks, and experiences) • Medications (including dose) & Health care utilization • Community program utilization (including barriers & facilitators) • Knowledge, Skills, Attitudes, Self-efficacy • Food Frequency Questionnaire [68] • Demographics: Race/ethnicity, age of child and parent, sex and gender identity of child and parent, address, zip code, birthplace, current employment status, educational attainment, annual family income, health insurance • SDOHfactors: Food insecurity, health literacy & numeracy, access to health services, access to health technology, internet access, job insecurity, housing insecurity, discrimination, discrimination in health care, food swamp	Ch P P Ch P P P P, Ch P	EHR Survey Survey EHR Survey Survey Survey Survey, EHR Survey	0, 6, 12 mos 0,12 mos 0,12 mos 0,12 mos 0,12 mos 0, 6, 12 mos 0, 6, 12 mos 0 mos 0, 12 mos

The PRISM Fit Assessment [72–74] will be conducted before each new roll-out of a clinic which examines how well the current implementation strategies align with the new clinic and whether it will reach similar RE-AIM metrics as in the previous clinic implementation. Representative clinic providers and staff, community stakeholders and hospital administrators will complete this 21-item survey using the iPRISM web tool (prismtool.org) before each clinic roll-out. Results will be reviewed during a CARAB meeting and additional refinements to the implementation strategy will be made.

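### The >81% power claim for Aim 3 is not supported for HbA1c, lipids and liver tests, because its 20% allowance covers loss to follow-up and not tests that were never ordered

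*Protocol article*

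**What the plan says.** **Source and timing.** The Medical record abstraction section states: "EHR data will be used to track patient health outcomes (e.g., BMI, HbA1c, LFTs, cholesterol". The first Aim 3 row of Table 1 lists "Health outcomes: BMI/weight status, HbA1c, blood pressure, total cholesterol, HDL cholesterol, liver function, health status", measured on the child, with the EHR as data source, at 0, 6 and 12 months. No study-ordered blood sample is described. Medical record abstraction also counts laboratory orders among the health care utilization items: "adherence to appointments, ED visits, hospitalizations, lab orders, medications prescribed".

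**Population.** The clinics are "diabetes, gastroenterology, preventive cardiology, and severe asthma clinic" (Methods). Participants states: "we plan to recruit 240 parents of a child aged 0–18 attending one of the participating clinics (~60 per clinic". Entry rests on clinic attendance and a positive food-insecurity screen. No laboratory indication is required.

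**Analysis.** Specific Aim 3 calls the outcomes exploratory and refers to "health outcomes that may be similar across the different clinics: weight status, blood pressure (BP), lipids, HbA1c, and liver function tests". Under Quantitative data, changes in metabolic labs, blood pressure and BMI are described together for the 240 participants, using growth models with clinic as a covariate.

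**Power.** Power considerations reports a simulation in which more than 81% of growth models had a significant slope. It describes this as "power given proposed sample of 60 per clinic and allowance for 20% missing data" and concludes that power is sufficient for Aim 3, without separating outcomes. Missing data explains the 20% as loss to follow-up. The imputation described there is for covariates or confounders missing at 10% or less.

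**The concern.** Two different reasons for a missing laboratory value are treated as one. The first is that the child leaves the study; the 20% allowance covers this, and the reminders, navigator follow-up and telemedicine options act on it. The second is that the child stays but the test is not in the record because nobody ordered it. Nothing in the power statement covers that, and retaining a child by telemedicine does not by itself produce a blood result. With the EHR as the only named source and four different specialties, there is no stated basis for assuming that every retained child has every test.

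Two things are at stake. First, the article states a property of the design, power above 81%, that may not belong to the laboratory outcomes. Second, the results are meant to inform a fully powered Type 2 hybrid trial. A laboratory change presented as one effect in 240 children across four clinics could rest on a smaller and differently composed group, and the next trial would then be planned on an effect size attached to the wrong population.

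**Working it through.** **Inputs from the article.** 240 children, about 60 per clinic; 20% allowance; visits at 0, 6 and 12 months; d of at least 0.20; median slope 0.02 per month with estimate SD 0.01; alpha 0.05; stated power above 81%.

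**Assumptions.** Two-sided test; outcome SD of 1; equal clinics; standard error proportional to 1/√n; the stated 81% refers to d = 0.20 at 12 months. The serial correlation comes from pilot samples and is not given. The share of children with each test is not given either, so a range is shown.

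**Step 1: can the 81% be reproduced?** Not independently, because the correlation is missing. Read literally, 0.02/0.01 gives z = 2 and power Φ(2 − 1.96) = 0.52. Both figures are rounded, however. A slope of 0.20/12 = 0.0167 with a standard error of 0.0059 rounds to the same pair and gives 0.81.

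The children contributing after loss are 240 × 0.80 = 192. Under compound symmetry the standard error of the slope is √[(1 − ρ)/(72n)], where 72 = (−6)² + 0² + 6². With n = 192 and ρ = 0.523 this is √(0.477/13,824) = 0.00587, and 0.01667/0.00587 = 2.84, the value needed for 81% power (1.960 + 0.878 = 2.838). An AR(1) correlation of 0.72 gives the same power. The stated figure is thus compatible with about 192 children contributing each outcome.

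**Step 2: fewer children with the test.** If a share *a* of children has the test and 20% of those are lost, n = 240 × *a* × 0.80. The noncentrality is 2.838 × √(n/192), power is Φ(noncentrality − 1.96) plus a negligible opposite tail, and the effect detectable at 81% power is 0.20 × √(192/n).

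| Share with test | n | Noncentrality | Power at d = 0.20 | Detectable d |
|---|---|---|---|---|
| 100% | 192 | 2.838 | 0.81 | 0.20 |
| 75% | 144 | 2.458 | 0.69 | 0.23 |
| 50% | 96 | 2.007 | 0.52 | 0.28 |
| 25% | 48 | 1.419 | 0.29–0.30 | 0.40 |

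The 25% row equals one clinic's worth of children (60 × 0.80 = 48). A simulation with clinic intercepts, correlation 0.52 and 20% dropout gave 0.53 to 0.54 for the 50% row and 0.30 to 0.31 for the 25% row, in agreement with the formula.

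**Step 3: sensitivity to the anchor.** Taking the slope of 0.02 at face value implies 0.02 × 12 = 0.24 at 12 months. Power at that slope, calibrated to 0.81 at 192 children, falls in the same way (0.69, 0.52, 0.29–0.30), because only the ratio n/192 matters. The detectable effects scale up by 0.24/0.20 = 1.2.

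**Step 4: does the clinic covariate help?** A clinic main effect shifts the level of the outcome. It adds no information on change from a clinic where the test is not recorded.

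**The case against.** The strongest reply is that the decisive quantity is not in the article. No section says which clinic orders which test, how often or for whom, and a condensed article may omit study-ordered samples or visit schedules that the full protocol contains. The power statement is one generic figure and names no laboratory test. The outcomes are labelled exploratory and preliminary. Mixed models use incomplete series and are valid under missing-at-random given the modelled terms. The Participants section also plans medical conditions, BMI percentile and medications as covariates or moderators, so the plan goes beyond adjusting for clinic alone.

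Much of this stands. A reader might infer that the laboratory results will really come from one or two clinics, or mainly from children tested on suspicion whose later values drift down. The documents do not support either as fact; both rest on guesses about ordering practice. Nor do they support the inference that the whole Aim 3 power claim fails, since it can hold for BMI, blood pressure and surveys. The table above is a range of scenarios and not an estimate for this trial.

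What does not stand is that the exploratory label or the model removes the problem. The article itself states a power figure, the sample behind it and the meaning of its 20%, and applies them to Aim 3 without exception. Mixed models and covariates do not create values for children who were never tested.

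**Conclusion.** The point holds for the laboratory outcomes only. As written, the power above 81% is unsupported for HbA1c, lipids and liver tests, because its missing-data allowance covers loss to follow-up and leaves out tests never ordered. Any test recorded in fewer than all retained children falls below the stated figure under the Step 1 calibration.

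The size depends on availability, which is not stated. It also rests on 81% corresponding to 192 children at d = 0.20, on a constant standardized effect when fewer clinics contribute, and on the absence of study-ordered samples, which is inferred from the article naming the EHR alone. Because the article says more than 81%, the calibrated powers would be somewhat higher if the simulated figure was well above that.

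The finding does not extend to barring all pooling of laboratory results, or to discarding tests ordered for a clinical indication. Both are debatable trade-offs, and the second would need order-reason data that the article does not describe.

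**What to change.** 1. In Power considerations, limit the >81% statement to outcomes expected in nearly all children, such as BMI, blood pressure and surveys.
2. Count past EHR orders by test and clinic. Restate power or the detectable effect for each laboratory outcome at the resulting n, or label these outcomes descriptive.
3. Under Quantitative data, report laboratory change by contributing clinic with its n, for example through clinic-by-time terms, instead of as one four-clinic effect in 240 children.
4. Do not exclude indication-triggered tests from the analysis. At most, examine them in a sensitivity analysis if the order reason can be obtained.

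The cost is a small EHR query, some rewording, and less favourable stated power for the laboratory outcomes. No new samples or participants are needed.
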